**Figure 2 F2:**
[figure not shown]
New motor skill—serial reaction time task (SRTT). This figure shows how SRTT will be used as a new motor skill during hand training sessions in this study. Numbers from 1 to 5 will appear on a computer screen and the subjects will be instructed to press the key with the finger that corresponds to that number as fast as possible. After a button is pushed, the number will disappear. The next number will be displayed 500 ms later. The learning test consists of 8 blocks (10 trials in each block). Each trial consists of 10 numbers which will appear with two types of sequence. In blocks 4 and 8 the sequence of numbers will be in a pseudo-random order in a way that each number will be presented equally frequently and never in the same order in two subsequent trials. In blocks 3, 5−7 as well as in blocks 9 and 10, the same sequence of numbers will be repeated 10 times (10 trials) (e.g., 2315243415). Subjects will not be told about the repeating sequence. SRTT, Serial Reaction Time Task; tDCS, Transcranial Direct Current Stimulation; TMS, Transcranial Magnetic Stimulation; CSE, Corticospinal excitability; SICI, Short Interval Cortical Inhibition; LICI, Long Interval Cortical Inhibition; ICF, Intracortical Facilitation; HFT, Hand Function Test; MSQOL, MS Quality of Life.

**Group 3: Experimental group (a-tDCS)** (*n* = 18): Patients in this group will participate in hand training sessions similar to Group 2 while they will receive a-tDCS on M1 area concurrently during the first 5 sessions of their hand training in week 1. The time frame for the assessments will be exactly the same as the previous groups.

**Group 4**: **Sham group** (*n* = 18): Patients in this group will participate in hand training sessions similar to Groups 2 and 3 while they will receive sham tDCS on M1 area concurrently during the first 5 sessions of their hand training in week 1. The time frame for the assessments will be exactly the same as the other groups.

### Rationale for the sample size

4.4.

The study is a within-subject, repeated measures study with one between factor (Group) with four levels and one within factor (Time) with seven time points. As we are predicting an effect size of 0.30 (medium to high), 16 subjects per group (a total of 64 subjects) is needed to achieve 80% power with a 5% significance level. Allowing for a 10% drop out rate, each group will need 18 subjects.

### A-tDCS intervention

4.5.

A DC-Stimulator (neuroConn. DC Stimulator plus) will be used to deliver 1 mA current to the M1 area via two surface electrodes with pockets of saline soaked sponges (0.9% NaCl). Active electrode (anode) measuring 3 × 4 cm will be placed over the left C3 or C4 according to the International 10–20 EEG system for electrode placement. The return (cathode) electrode (5 × 7) will be placed over contralateral supraorbital area. Participants will receive within-session repeated a-tDCS or sham tDCS paradigm (10-25-10 protocol) for 5 consecutive days. 10-25-10 protocol involves 10 min of tDCS intervention, followed by 25 min of rest, and then a further 10 min tDCS. The stimulator software has a study mode for blinding purposes that encodes sham and active stimulation parameters and can be set individually using the software. The safety and feasibility of this protocol and also its long-lasting effect in these patients have been assessed in our previous study (36).

#### Hand training session for group 1

4.5.1.

The patients in this group will be assessed by a physiotherapist and an individualized hand training program will be written based on the current practice standard.

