### Participants

4.2.

Seventy two patients with secondary progressive MS will be recruited. These patients will be assessed by a rehabilitation physician against the inclusion and exclusion criteria. Eligible participants will then be enrolled in the study.

**Inclusion criteria: (**a) 18 years of age and over; (b) secondary progressive MS; (c) impaired dominant hand functions (right side); (d) EDSS = 3–6 and (e) able to understand, speak and write in English.

**Exclusion criteria:** (a) skin conditions (e.g., eczema, lesions) on scalp; (b) metal inside the head (outside the mouth) such as shrapnel, surgical clips, or fragments from welding or metalwork; (c) any implanted devices such as cardiac pacemaker, cochlear implant, medical pump, or intracardiac line; (d) frequent or severe headaches; (e) previous head injury and any other brain related disease and (f) pregnancy and breast feeding.

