**Figure 1 F1:**
[figure not shown]
Flow diagram of randomization, intervention and assessments. This figure shows the randomization of the participants into 4 groups and the allocated intervention and assessment sessions throughout the trial. MS: Multiple Sclerosis; tDCS: Transcranial direct current stimulation.

**Group 1: Control group** (*n* = 18): Patients in this group will participate in hand training sessions only based on the current standard in clinics for 8 weeks. During week 1 this will be provided in 5 sessions over 5 consecutive days (30 min with rest) and during weeks 2–8, participants will have 2 sessions per week. They will have the following assessments: baseline assessments (before training); assessments during hand training (week 1, at the end of 5 consecutive training sessions and end of week 2, 4, 6 and 8); and follow-up assessments (week 12).

**Group 2: Experimental group (Hand training only**) (*n* = 18): Patients in this group will participate in hand training sessions in the exact time frame as Group 1 but they will practice a new motor skill (Figure 2) during their hand training sessions. The time frame for the assessments will be exactly the same as for Group 1.

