#### Hand training session for groups 2–4

4.5.2.

The participants will be seated in front of a computer screen at eye level behind a response pad with four buttons (numbered 1–4) and will be instructed to push each button with a different finger of the right hand (Thumb for button 1, index finger for button 2, middle finger for button 3, ring finger for button 4 and little finger for button 5) (Figure 2).

Numbers from 1 to 5 will be appeared on a computer screen and the subjects will be instructed to press the key with the finger that corresponds to that number as fast as possible. After a button is pushed, the number will disappear. The next number will be displayed 500 ms later. The learning test consists of 8 blocks (10 trials in each block). Each trial consists of 10 numbers which will appear with two types of sequence. In blocks 4 and 8 the sequence of numbers will be in a pseudo-random order in a way that each number will be presented equally frequently and never in the same order in two subsequent trials. In blocks 3, 5–7 as well as in blocks 9 and 10, the same sequence of numbers will be repeated 10 times (10 trials) (e.g., 2315243415). Subjects will not be told about the repeating sequence.

This study will enable the investigation of the effect of learning a new motor skill in M1 in patients with MS on improvement of hand functions compare to the current hand training programs. It will also enable the investigation of the lasting effects of multiple applications of a-tDCS on cortical excitability of M1 area in patients with MS which can facilitate the motor skill learning process and in turn increase the functional outcome of the hand training sessions (Figure 3).

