### Neurophysiological changes

6.1.

Changes in the cortical excitability, intracortical inhibitory (GABAergic) and excitatory (glutamergic) interneurons in M1 area will be assessed by single or paired-pulse transcranial magnetic stimulation (TMS) (Magstim Bistim^2^) in a block of 20 stimuli. The motor evoked potentials (MEPs) will be recorded from the right first dorsal interosseous (FDI) muscle. To measure the resting motor threshold (RMT), MEP threshold will be tested in steps of 2% maximum stimulator output, and defined as the lowest intensity for which three of five successive MEPs exceed 50 µV (rest) peak-to-peak amplitude (40).

To assess the overall cortical excitability of M1, recruitment curve will be produced by single pulse TMS and a range or suprathreshold intensity (0.6 × RMT–1.2 × RMT).

Paired-pulse TMS will be used to deliver two pulses with interstimulus interval of 3 ms, 10 ms or 150 ms through a figure of eight coil to assess the function of the intracortical inhibitory (GABAergic) and excitatory (glutamergic) interneurons respectively. This inhibition or facilitation are termed short interval intracortical inhibition (SICI), Long interval intracortical inhibition (LICI) or intracortical facilitation (ICF). The first stimulus for measuring SICI and ICF is subthreshold (0.8 x resting motor threshold: conditioning stimulus), however, it is suprathreshold [strong enough to produce 0.8–1.2 mV MEP (peak to peak)] for measuring LICI. The second pulse is suprathreshold for all conditions {[strong enough to produce 0.8–1.2 mV MEP (peak to peak): test stimulus]} for producing MEPs in the right FDI.

The first pulse that is subthreshold or suprathreshold for a motor response in right FDI, activates the inhibitory or facilitatory circuits and reduces or increases the size of the MEPs elicited by a supra-threshold test TMS pulse delivered 3 ms, 10 ms or 150 ms later to measure SICI, ICF and LICI respectively (41). The area of the conditioned and unconditioned MEPs will be measured from the averaged rectified MEPs obtained in each trial (42). The size of the conditioned MEPs will be expressed as a percentage of the unconditioned test MEPs in order to assess the effectiveness of SICI and ICF.

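### The anode site is given as left C3 or C4, which contradicts itself and the right-hand design; secondarily, the 45-minute stimulation schedule is not reconciled with the 30-minute session

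*Protocol article*

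**What the plan says.** **Site.** Section 4.5 (A-tDCS intervention) states that the anode "will be placed over the left C3 or C4 according to the International 10–20 EEG system for electrode placement". The return electrode "will be placed over contralateral supraorbital area", so its side follows from whichever side the anode takes.

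Three other sections name one hand. Section 4.2 requires "impaired dominant hand functions (right side". Section 4.5.2 says that participants in Groups 2–4 "will be instructed to push each button with a different finger of the right hand". Section 6.1 says that the MEPs "will be recorded from the right first dorsal interosseous (FDI) muscle".

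**Timing.** Section 4.5 describes each day's stimulation as "10 min of tDCS intervention, followed by 25 min of rest, and then a further 10 min tDCS". Section 4.3 gives Group 1 in week 1 "5 sessions over 5 consecutive days (30 min with rest"; this is the only session length stated. The same section ties Group 2's sessions to Group 1's timing. Group 3 trains in a similar way to Group 2 "while they will receive a-tDCS on M1 area concurrently during the first 5 sessions of their hand training in week 1", and Group 4 does the same with sham.

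**The concern.** Hypotheses 2 and 3 in Section 3.1 concern stimulation of the primary motor cortex (M1) in combination with learning a hand skill. To test them, the plan has to fix which M1 is stimulated and when the current flows relative to practice. As written, it fixes neither clearly.

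If the wording on site were followed literally, Group 3 could contain participants stimulated over different hemispheres, some of them over the M1 that does not control the trained hand. The group would then average over two interventions. In those stimulated on the other side, the cortical excitability, inhibition and facilitation measures from the right hand muscle would not describe the stimulated cortex.

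If stimulation outlasts the training session, part of it is not concurrent with training. If the session is lengthened to hold it, Group 3 may differ from Group 2 in session length or practice spacing as well as in stimulation.

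**Working it through.** The plan gives no figure on this point to reproduce. The check sets the sections side by side and does interval arithmetic on the timetable.

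**1. Site**

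| Item | Section | Side |
|---|---|---|
| Anode | 4.5 | Left C3 or C4 |
| Return electrode | 4.5 | Opposite to the anode, so also open |
| Eligible hand | 4.2 | Right |
| Trained hand, Groups 2–4 | 4.5.2 | Right |
| MEP recording | 6.1 | Right |
| Trained hand, Group 1 | 4.5.1 | Not stated (individualized program) |
| 9-hole peg test | 5.1 | Both hands |

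In the 10–20 system that Section 4.5 invokes, C3 is on the left and C4 on the right. The side word and the pair of sites therefore cannot both stand. Two sites would make sense if the target hand varied between participants, but the hand for eligibility, task training and MEP recording does not vary. No section gives a condition for using C4.

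**2. Length of the stimulation schedule**

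Elapsed time: 10 + 25 + 10 = 45 min. Current on: 10 + 10 = 20 min. Excess over a 30-min session: 45 − 30 = 15 min.

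**3. Overlap if the session is one continuous 30-min block (assumption)**

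Put the stimulation periods at 0–10 and 35–45 min, and let training run from s to s + 30.

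- A block that touches both periods must span the whole 25-min gap, which leaves 30 − 25 = 5 min for stimulation.
- A block that touches only one period can cover at most 10 min of it.

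| Start s (min) | Overlap with 0–10 | Overlap with 35–45 | Total |
|---|---|---|---|
| 0 | 10 | 0 | 10 |
| 5 | 5 | 0 | 5 |
| 10 | 0 | 5 | 5 |
| 15 | 0 | 10 | 10 |

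The maximum over all start times is 10 of 20 stimulation minutes (50%). At least 20 of the 30 training minutes are then without current.

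**4. Overlap if 30 min means practice time, with rest added (alternative assumption)**

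Let practice fill both stimulation periods (20 min) and 10 min of the gap: 20 + 10 = 30 min of practice and 25 − 10 = 15 min of rest, 45 min in all. All 20 stimulation minutes then coincide with practice. This reading fits, but Section 4.5 calls the gap rest and does not say whether practice continues in it. No section says whether Groups 1–2 are spread over 45 min in the same way.

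**The case against.** **On site**, the right-hand text elsewhere makes it likely that one hemisphere is intended, so this may be a slip of wording that staff would resolve in practice. That is plausible. But the sentence is the only definition of where the active treatment is applied, and read literally it permits either side.

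A reader might infer that Groups 3–4 may not receive M1 stimulation at all. The document does not support that: C3 and C4 both lie over a motor cortex, and only the hemisphere is in doubt. Nor is the whole design confined to the right hand, since the peg test is timed for both hands and Group 1's trained hand is not stated.

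**On timing**, the objection is stronger. The 30 min is written for Group 1 in week 1 only. It reaches the other groups through wording that could mean the same calendar of sessions rather than the same minutes, and similar is not identical. The text does not say the session is continuous, and step 4 shows a reading that fits. Figures 2 and 3 are not visible and may show the timetable; fine detail of this kind is also often left to a full protocol. So a reader who concludes that concurrent stimulation is impossible goes too far. What stands is that the printed durations do not add up on their plain reading and the text does not reconcile them.

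**On bias**, Groups 3 and 4 share the same site wording and schedule, so neither ambiguity by itself biases active against sham. The possible harm to that contrast is dilution. A difference in session length would affect comparisons of Groups 3–4 with Groups 1–2, and only if the sessions do in fact differ.

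**Conclusion.** The site wording is a defect in the definition of the intervention. It contradicts itself, and it does not fit the right-hand eligibility, task training and MEP recording. This conclusion needs no assumption beyond the 10–20 convention that the section itself cites. If both sites were used, and if the effect on the trained hand depends on the hemisphere, Group 3 v Group 4 and Group 3 v Group 2 would both be diluted.

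It is tempting to express that loss in standard deviations using the effect size of 0.30 in Section 4.4. The document does not support this: it gives no pattern of group means behind the 0.30, and nothing on what share of participants might be stimulated over the other hemisphere.

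The timing discrepancy is real but secondary. The 50% limit on concurrent stimulation holds only if the session is one continuous 30-min block that also applies to Groups 3–4. If those groups run for 45 min instead, comparability with Groups 1–2 in session length or spacing is the open question. It concerns only the five sessions of week 1, the only ones with stimulation.

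**What to change.** Reconcile Section 4.5 with Sections 4.2, 4.3, 4.5.2 and 6.1:

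- State one anode-location rule, consistent with the hand named for eligibility, training and MEP recording, and apply it identically to Groups 3 and 4. The side of the return electrode then follows.
- State one week-1 session timetable in which training, rest and both stimulation periods add up. Say whether practice continues between the two stimulation periods, and whether Groups 1–2 follow the same timetable.

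Which site and which timetable are right is for the investigators to decide.

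The cost is mainly protocol wording. If one timetable is applied to all groups, some week-1 sessions in Groups 1–2 may run longer. The change should come before participants are stimulated, because mixed delivery cannot be undone afterwards.

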#### Hand training session for groups 2–4

4.5.2.

The participants will be seated in front of a computer screen at eye level behind a response pad with four buttons (numbered 1–4) and will be instructed to push each button with a different finger of the right hand (Thumb for button 1, index finger for button 2, middle finger for button 3, ring finger for button 4 and little finger for button 5) (Figure 2).

Numbers from 1 to 5 will be appeared on a computer screen and the subjects will be instructed to press the key with the finger that corresponds to that number as fast as possible. After a button is pushed, the number will disappear. The next number will be displayed 500 ms later. The learning test consists of 8 blocks (10 trials in each block). Each trial consists of 10 numbers which will appear with two types of sequence. In blocks 4 and 8 the sequence of numbers will be in a pseudo-random order in a way that each number will be presented equally frequently and never in the same order in two subsequent trials. In blocks 3, 5–7 as well as in blocks 9 and 10, the same sequence of numbers will be repeated 10 times (10 trials) (e.g., 2315243415). Subjects will not be told about the repeating sequence.

This study will enable the investigation of the effect of learning a new motor skill in M1 in patients with MS on improvement of hand functions compare to the current hand training programs. It will also enable the investigation of the lasting effects of multiple applications of a-tDCS on cortical excitability of M1 area in patients with MS which can facilitate the motor skill learning process and in turn increase the functional outcome of the hand training sessions (Figure 3).

**Figure 3 F3:**
[figure not shown]
Timeline for intervention and assessments for one participant. This figure shows the timeline for the allocated intervention and assessment sessions for a participant in this study. Baseline assessment will be completed for each participant and then they start the hand training sessions ± tDCS intervention (5 sessions during week 1). During weeks 2−8, participants will have 2 hand training sessions per week. Then at the end of weeks 1, 2, 4, 6, 8 and 12, they will go through some post-intervention assessments or follow-up assessments.

#### Blinding

4.5.3.

Participants in Groups 3 (experimental a-tDCS) and 4 (sham tDCS) will be blinded as to the tDCS intervention they will receive. The treatment/sham mode will be set through the software based on the group allocations.

## Assessments: primary outcome measure

5.

### Manual dexterity: 9 hole peg test (9-HPT)

5.1.

The 9-HPT is considered as a gold standard measure of manual dexterity and most frequently used in MS research and clinical practice (37). During this test patients will sit behind a desk and will be instructed to pick up one peg at the time from the container and place it in a hole as fast as they can, then take them off and put them back to the container again. Their completion time will be recorded for both hands in two consecutive trials.

### Action research arm test (ARAT)

5.2.

The Action Research Arm Test (ARAT) is a comprehensive assessment tool for evaluating upper limb function. The test takes around 10 min to administer.

The test consists of 19 items grouped in 4 categories: grasp, grip, pinch, and gross arm movement. Each item is rated on a 4-point scale ranging from 0 (no movement possible) to 3 (movement performed normally). The maximum achievable score is 57 (38).

### Impact on participation and autonomy

5.3.

Impact on Participation and Autonomy questionnaire is used to measure how an individual perceives their level of autonomy and participation in various domains, including outdoor autonomy, indoor autonomy, family role, social relations, and paid work/education. It evaluates both the perceived level of participation and the presence of problems in each domain (39).

## Secondary outcome measures

6.

### Neurophysiological changes

6.1.

Changes in the cortical excitability, intracortical inhibitory (GABAergic) and excitatory (glutamergic) interneurons in M1 area will be assessed by single or paired-pulse transcranial magnetic stimulation (TMS) (Magstim Bistim^2^) in a block of 20 stimuli. The motor evoked potentials (MEPs) will be recorded from the right first dorsal interosseous (FDI) muscle. To measure the resting motor threshold (RMT), MEP threshold will be tested in steps of 2% maximum stimulator output, and defined as the lowest intensity for which three of five successive MEPs exceed 50 µV (rest) peak-to-peak amplitude (40).

To assess the overall cortical excitability of M1, recruitment curve will be produced by single pulse TMS and a range or suprathreshold intensity (0.6 × RMT–1.2 × RMT).

Paired-pulse TMS will be used to deliver two pulses with interstimulus interval of 3 ms, 10 ms or 150 ms through a figure of eight coil to assess the function of the intracortical inhibitory (GABAergic) and excitatory (glutamergic) interneurons respectively. This inhibition or facilitation are termed short interval intracortical inhibition (SICI), Long interval intracortical inhibition (LICI) or intracortical facilitation (ICF). The first stimulus for measuring SICI and ICF is subthreshold (0.8 x resting motor threshold: conditioning stimulus), however, it is suprathreshold [strong enough to produce 0.8–1.2 mV MEP (peak to peak)] for measuring LICI. The second pulse is suprathreshold for all conditions {[strong enough to produce 0.8–1.2 mV MEP (peak to peak): test stimulus]} for producing MEPs in the right FDI.

The first pulse that is subthreshold or suprathreshold for a motor response in right FDI, activates the inhibitory or facilitatory circuits and reduces or increases the size of the MEPs elicited by a supra-threshold test TMS pulse delivered 3 ms, 10 ms or 150 ms later to measure SICI, ICF and LICI respectively (41). The area of the conditioned and unconditioned MEPs will be measured from the averaged rectified MEPs obtained in each trial (42). The size of the conditioned MEPs will be expressed as a percentage of the unconditioned test MEPs in order to assess the effectiveness of SICI and ICF.

